**Fig. 3 Fig3:**
[figure not shown]
Trial procedure flow sheet

### Safety

Vitamin D deficiency treatment is required for patients with low vitamin D levels (< 20 ng/ml) [1]. However, the primary side effect of cholecalciferol supplementation is hypercalcemia [13]. To prevent hypercalcemia in TBI patients, serum vitamin D and calcium levels are evaluated regularly; as adequate vitamin D levels are reached, hypercalcemia is likely to be treated; therefore, the intervention will be stopped [23]. Moreover, to keep track of the patient’s condition, daily vital signs and clinical examinations by neurosurgeon and ICU supervisor will be carried out and will be stopped if the patient’s condition deteriorates.

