**Methods/design:**

A randomized clinical trial (RCT) will be performed on 74 Iranian adults 18–65 years old with brain trauma and will be treated daily with vitamin D supplements (100,000 IU oral drop) or a similar placebo (1000 IU) for 5 days.

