### Study design and setting

We will include 74 TBI patients with epidural hemorrhage (EDH), subdural hemorrhage (SDH), and subarachnoid hemorrhage (SAH) as diagnosed according to computed tomography (CT) scan or magnetic resonance imaging (MRI) findings by the neurosurgeon. Patients will receive vitamin D (cholecalciferol) drop (100,000 IU) or 1000 IU identical control drop in a 1:1 ratio through random assignment method. Vitamin D drops are manufactured by Zahravi Company under good manufacturing practice (GMP). Each vial of vitamin D drop is produced to be dissolved completely in 1 ml of extra virgin olive oil (Familia Company), through a nasogastric tube (NGT) for 5 days in TBI patients. Both high-dose and low-dose drops will have the same bottle, flavor, and aroma to the blinded.

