### Sample size

To calculate the sample size, in accordance with a previous study [7], interleukin 6 (IL-6) will be used as the main variable and the type 1 error is considered with an alpha of 0.05. We estimated 62 TBI patients with 80% power to detect an effect size of 0.5 for reduction of IL-6 between the intervention and control groups as calculated with the formula shown below. Considering 20% dropouts in this study, the total sample size is estimated to be 37 participants in each group as calculated in the below formula [7]:
$$ \frac{\left(Z1-\frac{\alpha }{2}+Z1-\beta \right)2\ \left(\delta 12+\delta 22\right)}{\left(\upmu 1-\upmu 2\right)2} $$

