### Proposed analysis

To determine the normal distribution of variables, the Kolmogorov-Smirnov test will be conducted. The analysis will be performed according to the intention-to-treat (ITT) test. We perfomed an independent t-test or the Mann-Whitney test for continuous variables and the chi-square or Fisher exact test for categorical variables. Repeated measure one-way analysis of variance (ANOVA) or multivariable covariance analysis (ANCOVA) will be conducted to examine differences in severity of brain injury score (GCS), APACHE II score, SOFA score, delirium score, and all variables at study baseline between the two groups. Kaplan-Meier test was conducted and compared with the use of the log-rank test for estimates of survival time. The *P* values less than 0.05 will be considered statistically significant.

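### Therapeutic vitamin D given after randomisation is a ground for exclusion, which is likelier to remove controls and conflicts with the intention-to-treat analysis

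*Protocol article*

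**What the plan says.** All references are to the protocol article.

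- **Inclusion criteria:** every participant has 25(OH)D below 20 ng/ml.
- **Safety:** for levels below 20 ng/ml, "Vitamin D deficiency treatment is required for patients with low vitamin D levels", with a literature reference. The same paragraph says that "serum vitamin D and calcium levels are evaluated regularly" and that the intervention stops once levels are adequate.
- **Study design and setting:** "Patients will receive vitamin D (cholecalciferol) drop (100,000 IU) or 1000 IU identical control drop in a 1:1 ratio". The abstract words the control as "or a similar placebo (1000 IU) for 5 days", whereas the Background and the objectives call it low-dose vitamin D.
- **Non-entry criteria:** counting down the list, the fifth entry is treatment with vitamins or minerals at therapeutic doses, with an exemption for whatever the unit's routine protocol provides.
- **Exclusion criteria:** items 1 to 5 of that list are also grounds for exclusion. The other entries are death within the first 7 days, a family request to stop, and a different medication protocol.
- **Proposed analysis:** "The analysis will be performed according to the intention-to-treat (ITT) test".
- **Study assessments and Primary efficacy endpoint:** 25(OH)D and the inflammatory markers are measured at baseline and on days 7 and 14; mortality is followed to day 28. Drugs ordered during the ICU stay are recorded.

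**The concern.** A rule that no patient may be on therapeutic vitamins is sound at entry. Once it runs after randomisation, it turns a treatment decision into a reason to leave the trial. That decision is tied to the randomised treatment: what would prompt corrective vitamin D is persisting deficiency, and correcting deficiency is what the two doses are meant to do differently. Losses from this rule would therefore not be expected to balance between arms.

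The comparisons at stake are the day-7 and day-14 markers and 28-day mortality. If patients leave them for a reason that follows from their allocation, the remaining groups are no longer the randomised groups.

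**Working it through.** **Step 1. Does the fifth criterion act after randomisation?** The Exclusion criteria are separate from the Non-entry criteria and include death in the first week and a request to stop, which can only occur once a patient is in the trial. Their reference to items 1 to 5 therefore covers vitamin D given after entry. The item number comes from counting the list.

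**Step 2. Is it likely to fall evenly?** Trial vitamin D over the course:

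- high dose: 5 × 100,000 = 500,000 IU
- control: 5 × 1,000 = 5,000 IU
- ratio: 500,000 / 5,000 = 100

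All patients start below 20 ng/ml, so those still deficient at a later measurement should mostly be controls. This is an inference from the doses; the article gives no data on response.

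**Step 3. What could it do to 28-day mortality?** The article gives no rate of non-study vitamin D and no expected mortality, so every input here is an assumption. Suppose no true effect, 37 per arm and 9 deaths in each (9/37 = 24.3%). Suppose 8 controls with 1 eventual death, or 15 controls with 2, are given corrective vitamin D after day 7.

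*If intention-to-treat governs:* 9/37 against 9/37, difference zero.

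*If the Exclusion criteria govern:* deaths before day 7 are removed from both arms as well. With e early deaths per arm, the high-dose arm is (9 − e)/(37 − e). The controls are (9 − e − 1)/(37 − e − 8) or (9 − e − 2)/(37 − e − 15).

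| Early deaths per arm | High dose | Control, 8 removed | Control, 15 removed | Difference, control minus high dose (points) |
|---|---|---|---|---|
| 4 | 5/33 = 15.2% | 4/25 = 16.0% | 3/18 = 16.7% | +0.8 to +1.5 |
| 5 | 4/32 = 12.5% | 3/24 = 12.5% | 2/17 = 11.8% | 0 to −0.7 |
| 6 | 3/31 = 9.7% | 2/23 = 8.7% | 1/16 = 6.3% | −1.0 to −3.4 |

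The sign turns on the split between early and late deaths, which the article does not give.

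**Step 4. What could it do to the markers?** Suppose the worst fraction q of controls, on a factor correlated ρ with the marker, is removed. The control mean then shifts by ρ × φ(z)/(1 − q) SD in the favourable direction, where z is the 1 − q normal quantile and φ the normal density. For q = 0.10 and ρ = 0.2 this is 0.04 SD; for q = 0.30 and ρ = 0.4 it is 0.20 SD. That would understate a benefit of high dose. If the patients removed were the less inflamed ones, the shift would go the other way. Nothing in the article says which applies.

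**The case against.** Three stronger readings are tempting, and the document supports none of them.

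*That the protocol leaves controls untreated against its own safety requirement.* The sentence in Safety is a referenced general statement that introduces a paragraph on preventing hypercalcaemia. It sets no dose, timing or trigger for the trial. Controls do receive 1000 IU a day. Repletion under the routine ICU protocol is exempt from exclusion, so a deficient control does not have to be either neglected or lost. Whether routine care includes repletion is not stated.

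*That the rule inflates control mortality and favours high dose.* A reader might argue that anyone treated on a day-7 result has survived to day 7, so excluding such patients takes survivors out of the control denominator. With the assumptions above that gives 8/29 = 27.6% to 7/22 = 31.8% against 24.3%, about 3 to 7 points. But it applies only part of the exclusion list: early deaths are excluded under the same heading. Once they are removed too, the gap shrinks, vanishes or reverses, and under intention-to-treat it is zero.

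*That a rescue rule for deficiency after day 5 is missing.* A condensed article commonly leaves such a rule to the full protocol.

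It can also be said that researchers and nurses are blinded, that no section links a day-7 result to open-label vitamin D, and that the intention-to-treat statement may override the exclusions. Blinding helps only in part, because a low measured value could prompt treatment without knowledge of the allocation. The intention-to-treat statement does not say how excluded patients are handled, and it cannot restore blood samples not taken once a patient has been withdrawn. What stands is the narrower point: the exclusion route exists, it is likelier to affect controls, and it is not reconciled with the stated analysis.

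**Conclusion.** The point holds in limited form. The Exclusion criteria make non-routine therapeutic vitamin D after randomisation a ground for removal, all participants enter at a level that the article itself says needs treatment, and the arms differ 100-fold in dose. That is a treatment-related exclusion after randomisation, and it conflicts with the intention-to-treat analysis.

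No size or direction can be given. The mortality differences of −3.4 to +1.5 points and the marker shifts of 0.04 to 0.20 SD show only what assumed rates could do. The unequal effect on the arms rests on the dose difference, and on some patients receiving vitamin D outside routine care. If none did, nothing is lost.

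**What to change.** Apply the fifth non-entry criterion at entry only, and remove it from the grounds for exclusion. State that vitamin D given after randomisation does not end participation or remove data. Analyse all patients as randomised for the day-7 and day-14 markers and for 28-day mortality. Report non-study vitamin D (date and dose) by arm, so that the results can be read with that exposure in view.

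The article reports recruitment as complete, so for this trial the change is mainly to the analysis and reporting. For anyone already excluded under this item, 28-day vital status should be retrieved where possible, and marker samples not taken should be shown as missing by arm.

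The cost is a few lines of wording. Drug records already cover the ICU stay; exposure on the regular ward up to day 28 may need to be looked up. The one statistical price is that vitamin D given to controls may dilute the contrast, but the comparison stays randomised.

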### Non-entry criteria

Patients with hypercalcemia (Ca > 10.8 mg/dl)TBI patients who are NPO more than 48 h or have started total parenteral nutrition (TPN)Severe and active bleedingPatients treated with inotropic and corticosteroid drugsPatients treated with therapeutic dose of any vitamins and minerals apart from the routine ICU protocolPatients with body mass index (BMI) > 40 kg/m^2^ and BMI < 17 kg/m^2^History of any disease such as autoimmune disorders, cancer, sepsis, infection, liver disorder, kidney disorder, diabetes, heart failure, and metabolic diseasesKnown pregnancy and lactationPatients who are transferred from other ICUs after > 1 week

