### Study assessments

At the beginning of the trial, demographic information, anthropometric parameters (weight (bed scale, Balas Company), estimating height from ulna length), mid arm circumference (measured by tape at the mid-point between the tip of the shoulder and the tip of the elbow), fat-free mass and fat mass (bioelectrical impedance analysis s10, InBody Company), vitamin D3 status (25-hydroxy vitamin D3, chemiluminescence method), IL-6 (ELISA kit), MCP-1 (ELISA kit), quantitative CRP (ELISA kit), PTH (ELISA kit), Ca, APACHE II score, SOFA score, and delirium score will be measured and repeated on days 7 and 14 after intervention in groups A and B. All drugs will be ordered daily upon physician’s request during ICU stay and will be recorded. For adjusting the effect of energy on final outcomes, based on ESPEN guideline for all patients, 25 kcal/kg actual body weight energy is considered [21]. Moreover, the total kilocalories and macronutrient delivered by enteral feeding will be calculated daily for all the participants. Blood samples (5 ml) will be collected at baseline (ICU admission) and 7 and 14 days after intervention at 10:00 am. Blood sample will be taken from veins and centrifuged at room temperature, then stored at − 20 °C. Finally, the samples will immediately be transferred with the cold box to a freezer − 80 °C for future inflammatory cytokine measurements. All routine biochemistry, hematology, and urine tests, until day 14, will be measured after sampling in Kamyab Hospital Lab, Mashhad, Iran. Serum IL-6, MCP-1, and CRP levels will be analyzed in the baseline and days 7 and 14 at the Immunology Lab of Bu Ali Research Institute, Mashhad, Iran. In addition, in case of occurrence of infections (blood stream, the urinary tract, the gastrointestinal tract, wounds, and the lung), an internist specialist will take responsibility [22]. A summary of the schedule of registration, supplementation, and study evaluation is shown in Fig. 3.

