## Discussion

In the present study, if vitamin D significantly reduces the rate of mortality and inflammation in TBI patients, it can potentially provide the background for larger and well-designed multicenter clinical trial studies to establish the effect of vitamin D supplementation on TBI patients. Furthermore, vitamin D treatment is inexpensive and safe with minimal side effects and also could have positive impacts on critically ill patients (such as decreased mortality rate and hospital length) according to previous studies [7, 13, 14, 23, 24]. Potential limitations of the proposed study are as follows: measurement of vitamin D3 concentration with the chemiluminescence test instead of the gold standard method (liquid chromatography-tandem mass spectrometry). Another limitation is TBI patients’ blood transfusion because of trauma and bleeding; some TBI patients may require blood transfusion during the study, which may affect the biochemistry outcomes. Albumin injection in hypoalbuminemia patients can affect the levels of serum albumin. Also, TBI patients may need to undergo other surgeries than brain surgery; thus, this factor could affect the study outcomes. For this reason, we will compare mortality rate and inflammatory cytokine levels in all participants (intervention and control) and separate patients with anemia and hypoalbuminemia in each group. If the rate of death or inflammation in patients with anemia and hypoalbuminemia is different from those in the case or control group, the results will be reported separately. Based on recent studies, we have considered the suggested vitamin D dose (100,000 IU/day for 5 days) by Han et al. [23], as it is shown to be safe and efficacious in critically ill patients. Therefore, we believe that the present study could elaborate the necessity of vitamin D treatment and its efficacy on TBI patients at ICU.

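### Hypercalcaemia after entry is an exclusion criterion, which conflicts with the intention-to-treat analysis, differs from the Safety section, and could hide the drug's main side effect

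*Protocol article*

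**What the plan says.** Four sections of the protocol article bear on a high calcium value found after a patient has entered the trial.

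- **Non-entry criteria.** The first item is "Patients with hypercalcemia (Ca > 10.8 mg/dl").
- **Exclusion criteria.** This separate list names death before 7 days have passed, a family request to stop, treatment under a different medication protocol, and meeting any of non-entry items 1 to 5. The last entry brings calcium above 10.8 mg/dl back in as a reason for exclusion.
- **Safety.** Hypercalcaemia is introduced as the main harm of the drug: "However, the primary side effect of cholecalciferol supplementation is hypercalcemia". The stated consequence is: "as adequate vitamin D levels are reached, hypercalcemia is likely to be treated; therefore, the intervention will be stopped". Nothing is said there about whether the patient remains in the trial.
- **Proposed analysis.** "The analysis will be performed according to the intention-to-treat (ITT) test".

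Under Study assessments, calcium is in the set of baseline measurements that "will be measured and repeated on days 7 and 14 after intervention in groups A and B". Hypercalcaemia is not among the primary or secondary efficacy endpoints.

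**The concern.** An event that the study drug can cause should not decide who stays in the trial's data. Here the protocol names hypercalcaemia as the drug's primary side effect and also lists it as a ground for exclusion after entry. The arms receive 100,000 IU and 1000 IU daily, so such exclusions would be expected to fall more on the high-dose arm.

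Two things would be at stake. First, the side effect that the protocol itself singles out could be undercounted, because the patients who had it leave the data. Second, the same patients could lose their later observations: day-14 vitamin D and inflammatory markers and 28-day mortality status, all under the primary efficacy endpoint, and day-14 PTH, which is secondary. Losses that depend on treatment undo part of what randomisation provides.

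**Working it through.** The article gives no figure to reproduce, so the main check sets the sections side by side. An illustration of size follows.

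**1. Does the exclusion list apply after entry?** Yes. It is kept apart from the non-entry list, and it contains early death and family withdrawal, which can only happen once a patient is in the trial.

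**2. What does exclusion mean?** The article does not define it. Early death is the best clue. A patient who has died has no treatment left to stop, so that entry makes sense only as removal from the study or the analysed set. Hypercalcaemia sits in the same list with no different consequence attached.

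**3. Against Proposed analysis.** Intention to treat keeps all randomised patients in their assigned arm. Removing a patient for an event after randomisation is incompatible with that.

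**4. Against Safety.** That section says "therefore, the intervention will be stopped" and is silent on participation. Its trigger is also unclear: the sentence can be read as adequate vitamin D being reached or as hypercalcaemia. The next sentence, on monitoring, "will be carried out and will be stopped if the patient’s condition deteriorates", does not make clear what is stopped; grammatically it is the examinations.

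**5. Timing.** Dosing lasts 5 days. The scheduled calcium values after baseline are on days 7 and 14. A case found at either visit comes after the last dose, so excluding the patient then ends no dosing and can only cost data.

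**6. Size (illustration only).** Inputs: 37 patients per arm (Sample size); hypercalcaemia rate p in the high-dose arm, not given in the documents and assumed to be 5% to 15%.

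Expected cases = 37 × p; probability of at least one case = 1 − (1 − p)^37.

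| Assumed p | Expected cases | Probability of at least one | High-dose cases seen if all are removed |
|---|---|---|---|
| 5% | 37 × 0.05 = 1.85 | 1 − 0.95^37 = 85% | 0 |
| 10% | 37 × 0.10 = 3.7 | 1 − 0.90^37 = 98% | 0 |
| 15% | 37 × 0.15 = 5.55 | 1 − 0.85^37 = 99.8% | 0 |

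So about 2 to 6 high-dose patients would be affected. If all were removed, the last column would be zero whatever the true rate.

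**The case against.** **The trial's safety conclusion.** A reader might infer that this trial's safety conclusion rests on patients who did not have the harm. The documents do not support that. They define no safety endpoint, safety population or safety conclusion from the trial's own data. The Discussion's statement that "vitamin D treatment is inexpensive and safe with minimal side effects" is attributed to previous studies, so exclusions here cannot bias it. No section says that excluded patients' calcium values or 28-day status are discarded, and intention to treat is stated. The participant flow diagram, not shown, may list exclusions with reasons. This stands, and it makes the bias conditional on what exclusion means.

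**Flat contradiction with Safety.** A reader might also take the Safety section to say that the patient stays in. It does not address participation, and stopping treatment and excluding the patient could both apply. The direct conflict is between the Exclusion criteria and intention to treat; the Safety section differs by describing a narrower consequence.

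**Timing.** The Safety section has calcium checked regularly, and routine biochemistry runs to day 14. A case could be found while dosing continues, so step 5 holds only for cases found at days 7 or 14.

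**Confidence limits.** It is tempting to argue that a zero count would rule out the actual rate. That depends on the assumed number of cases. The one-sided 95% upper limit for 0 of n is 1 − 0.05^(1/n).

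- 2 cases: 2/37 = 5.4%; limit for 0/35 is 8.2%.
- 3 cases: 3/37 = 8.1%; limit for 0/34 is 8.4%.
- 4 cases: 4/37 = 10.8%; limit for 0/33 is 8.7%.

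The limit falls below the proportion only from 4 cases upward, so no conclusion is rested on it. The documents also give no basis for claiming that the excluded patients would be the strongest PTH or vitamin D responders.

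**Conclusion.** The point holds in a limited form. Calcium above 10.8 mg/dl after entry is an exclusion criterion. That conflicts with the stated intention-to-treat analysis and goes further than the Safety section. This is an inconsistency in what the article states, and more than omitted detail.

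The possible harm to the results rests on two assumptions: that exclusion means leaving follow-up and analysis, which the listing beside early death makes the most natural reading, and that cases arise more often at the higher dose, for which there is no arm-specific figure. Under both, and with an assumed rate of 5% to 15%, about 2 to 6 of 37 high-dose patients would leave the data for a possible effect of treatment. The main harm could then be undercounted, and their day-14 and 28-day outcomes lost. The matter should be corrected, but the documents do not show that the reported results will be biased.

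**What to change.** Reconcile the Exclusion criteria, Proposed analysis and Safety sections by separating two decisions: stopping the intervention, and leaving follow-up and analysis.

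- Keep every randomised patient with hypercalcaemia after entry in the intention-to-treat set, in the assigned arm, with the day-14 and day-28 data already scheduled or collected.
- Report the number of patients with hypercalcaemia by randomised arm, using the calcium values already measured at baseline and on days 7 and 14.

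When and whether to stop the intervention remains the investigators' decision. The sections need only agree on what follows from it.

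Trial status reports recruitment completed on December 21, 2019, with procedures expected to end by late January 2020. The change therefore applies to the analysis set and the report; it cannot recover samples that were not taken. If any patient was excluded on this ground, the report should give the number by arm and state which later data are missing. The cost is a change of wording and a short table. The downside is that the reported side-effect rate may look less favourable.

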### Primary efficacy endpoint

The primary efficacy outcome for this trial will be assessed by comparing the changes in vitamin D levels and inflammatory markers (IL-6, monocyte chemoattractant protein-1 (MCP-1), and C-reactive protein (CRP)) between two groups. The rate of mortality in TBI patients until 28 days after admission (in ICU and regular ward) will be assessed in high- and low-dose vitamin D supplement groups. The impact of high dose versus low dose of vitamin D will be analyzed, with and without adjustment for age, sex, type of brain injury, and severity of injury. If the results differ after adjusting for the variables, the results of both analyses will be reported.

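### Excluding randomised patients for hypercalcaemia contradicts intention-to-treat, and the vitamin D stopping rule has no listed result to act on during dosing

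*Protocol article*

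**What the plan says.** All references are to the protocol article.

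**Calcium.** The first item under Non-entry criteria is "Patients with hypercalcemia", defined as calcium above 10.8 mg/dl. The Exclusion criteria then apply the first five non-entry items to patients already in the trial. They stand beside death before day 7 and a family's request to stop. Safety names hypercalcaemia as the primary side effect of cholecalciferol.

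**Analysis set.** Proposed analysis states: "The analysis will be performed according to the intention-to-treat (ITT) test".

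**Stopping the drug.** Safety says that "serum vitamin D and calcium levels are evaluated regularly" and continues: "as adequate vitamin D levels are reached, hypercalcemia is likely to be treated; therefore, the intervention will be stopped". It gives neither monitoring days nor a value for an adequate level.

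**Course and schedule.** Study drug is given "through a nasogastric tube (NGT) for 5 days in TBI patients". The Discussion describes the high dose as "100,000 IU/day for 5 days". Study assessments lists 25(OH)D and calcium among the baseline measurements that "will be measured and repeated on days 7 and 14 after intervention in groups A and B". It also mentions routine biochemistry until day 14, without naming its components.

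**Endpoint.** The primary efficacy endpoint includes "comparing the changes in vitamin D levels and inflammatory markers", and mortality to day 28 is assessed under the same heading.

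**The concern.** There are two linked faults in how the plan handles the drug's expected toxicity.

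The first is the more serious. An event that the study drug is expected to cause is used as a reason to take a randomised patient out of the trial. Patients removed this way would plausibly come mainly from the high-dose arm, so the two groups left for comparison would no longer be those that randomisation formed. The marker changes and 28-day mortality would then be compared between differently selected groups. The patients who suffered the main named harm would be missing from the results, so the high dose would look safer than it was.

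The second is that Safety, as worded, ties stopping to an adequate vitamin D level rather than to calcium. On the listed schedule no such result arrives while the drug is being given. If unlisted results were used, the rule would turn a fixed 5-day course into dosing to a target, mainly in one arm. The trigger would be a variable that is itself part of the primary endpoint.

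**Working it through.** The plan gives no figure of its own on this point to reproduce. The check is a comparison of sections followed by simple arithmetic.

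**Inputs from the protocol**
- 37 patients per arm (Sample size).
- 100,000 IU versus 1000 IU daily for 5 days (Abstract; Study design and setting; Discussion).
- All patients below 20 ng/ml at entry (Inclusion criteria).
- 25(OH)D and calcium at baseline and days 7 and 14 (Study assessments).
- Calcium limit 10.8 mg/dl (Non-entry criteria).

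**Inputs that are assumptions, because the protocol gives none**
- 1 to 4 high-dose patients excluded for calcium.
- 8 deaths among 37.
- 10%, 30% or 50% of the high-dose arm stopped after dose 3.
- A rise in 25(OH)D proportional to dose.

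**Step 1: exclusion against intention-to-treat.** Intention-to-treat keeps every randomised patient in the assigned arm. The Exclusion criteria remove some after entry. Both cannot hold unless exclusion means only that study drug ends, and the text does not say so. For calcium measured at the listed post-baseline visits, that reading does not help: day 7 falls after the last of five daily doses, so there is no drug left to stop. An exclusion at that visit could only remove the patient.

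**Step 2: effect on the mortality comparison.**
- Share of the arm removed: 1/37 = 2.7%; 4/37 = 10.8%.
- Mortality with nobody removed: 8/37 = 21.6%.
- Four removed, all of whom died: (8 − 4)/(37 − 4) = 4/33 = 12.1%.
- Four removed, none of whom died: 8/33 = 24.2%.
- If the true rate were 21.6% in both arms and only the high-dose arm lost patients, the apparent difference would run from 12.1 − 21.6 = −9.5 to 24.2 − 21.6 = +2.6 percentage points, with no treatment effect at all.

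**Step 3: can the vitamin D trigger act?** The dosing days are 1 to 5. The listed post-baseline 25(OH)D days are 7 and 14. Whether day 7 is counted from the first or the last dose, the number of listed results during dosing is 0.

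**Step 4: if unlisted in-course results were used.**
- Planned dose: 5 × 100,000 = 500,000 IU versus 5 × 1000 = 5,000 IU, a ratio of 100.
- If each 100,000 IU raises 25(OH)D by *r*, the full course gives 5*r* in the high-dose arm and 0.05*r* in the low-dose arm. All patients start below 20 ng/ml, so an adequacy threshold would be crossed mainly in the high-dose arm.
- A high-dose patient stopped after dose 2, 3 or 4 receives 200,000, 300,000 or 400,000 IU, which is 40%, 60% or 80% of plan.
- If a share *f* of the arm stops after dose 3, the mean dose is 500,000 − *f* × 200,000. For *f* = 0.1, 0.3 and 0.5 this is 480,000, 440,000 and 400,000 IU (96%, 88%, 80% of plan).

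**The case against.** The strongest case on the other side has four parts.

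*The schedule is not fully visible.* Figures 2 and 3 are not shown and may list in-course checks. Safety says monitoring was regular, and routine biochemistry may have covered calcium. An article may also leave monitoring days and the cut-off for adequacy to the full protocol. This stands. It is why the vitamin D part goes no further than saying that the text lists no in-course result.

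*The Safety sentence is garbled.* It opens with the aim of preventing hypercalcaemia, and the intended trigger may well have been calcium. That is plausible, and it supports restating the rule, because the published wording makes vitamin D adequacy the reason to stop.

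*Stopping a drug for safety is compatible with intention-to-treat.* This is correct. Stopping early dilutes exposure but does not change who is analysed. The objection here is to removing the patient, which the Exclusion criteria do.

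*Exclusion may mean only the end of treatment.* This cannot be ruled out. But the same list contains death before day 7 and family withdrawal, so it reads as removal from the trial, and nothing in the text says these patients' data are kept.

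A reader might also infer that doses were in fact cut in the high-dose arm alone, or that ICU staff learned the allocation from 25(OH)D results. The documents support neither. They record no stops, and they do not say that staff saw post-baseline values. Randomization and blinding restricts the allocation list to the research director. A stop on adequacy would fall mainly, not only, on the high-dose arm.

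**Conclusion.** The conflict between the Exclusion criteria and the intention-to-treat statement holds on the text. Its direction is plausible rather than demonstrated: the excluded event is the drug's main named side effect and the doses differ 100-fold. Its size cannot be fixed from the protocol. Under the assumed 8 deaths and 4 exclusions, the high-dose mortality rate could be reported anywhere from 12.1% to 24.2% against 21.6% with everyone kept. The lower end requires all four excluded patients to have died.

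The vitamin D stopping rule is a lesser fault. As worded it has no listed result to act on, so either it did nothing or it worked from checks that the text does not list. In the second case, mean high-dose exposure would be 80% to 96% of plan if 10% to 50% of that arm stopped after dose 3. The number of stops and any effect on blinding remain unknown.

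This should be corrected, with most weight on the analysis set. The exclusion of deaths before day 7 in the same list is a separate matter, and none of these figures depend on it.

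**What to change.** 1. **Exclusion criteria.** Make the calcium limit a reason to end study drug, not participation. Suggested text: *Serum calcium above 10.8 mg/dl after entry ends study drug. These patients stay in follow-up to day 28 and are analysed in their assigned arm.*
2. **Safety.** Replace vitamin D adequacy as the trigger with the protocol's own calcium limit of 10.8 mg/dl, subject to clinical confirmation.
3. **Reporting.** Tabulate hypercalcaemia, early stops and doses received by arm.
4. **Disclosure.** State which in-course calcium and 25(OH)D checks were done and who saw the results.

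Trial status says recruitment closed on December 21, 2019, so a new stopping rule can no longer change how these patients were dosed. Item 2 now serves to correct the record. What can still change is the analysis set, the by-arm reporting and the monitoring statement. Patients already excluded should be restored to their arm, with day-28 status included wherever it is available.

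The cost is one sentence on the analysis set, one table and one statement on monitoring, with no new patients or measurements. The price under intention-to-treat is some diluted exposure in the high-dose arm, which the table of doses received would make visible.
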